**METHODS**

**Design**

This will be a double-blind sham-controlled two-arm randomized clinical trial. Fifty participants will be randomized (1:1) to each arm. Arm 1 will be active tDCS plus varenicline (n=25) and Arm 2 will be sham tDCS plus varenicline (n=25). Treatment duration will be 12 weeks. Subjects will be required to attend an in person assessment visit. They will then be randomized to a condition. Neuroimaging scans (fMRI) and eye-tracking tests will be conducted in all participants at baseline. Participants will undergo two scans at baseline on different days within the same week: one in a satiated state and one in a non-satiated state. The same tasks will be performed at each scan. s. Following the baseline fMRI scans and eye-tracking tests, subjects will start taking the varenicline simultaneous with starting the tDCS regimen whereby they will come to the clinic every day (Monday to Friday) for the first 2 weeks to undergo the stimulation (active: 20 minutes at 2mA, sham: 30 seconds at 2mA and then nothing). Their target quit date will be at the end of this 2 week period. They will return to the clinic every two weeks for the next 10 weeks for a booster tDCS session and to complete questionnaires. Eye tracking tests will be conducted at the end of the fourth and eighth weeks. At the end of the 12-week treatment period they will undergo a third fMRI scan and eye-tracking tests. For the next 14 weeks they will be contacted weekly by e-mail or text message to report on their smoking status as measured by the 7 day point prevalence abstinence question. “Have you had a cigarette, even a puff, in the last 7 days?” At the 6-month time point subjects will be asked to return to the clinic for a brief visit to confirm smoking abstinence using expired CO and urinary cotinine and to complete questionnaires.

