**Outcome Measures**

The primary outcome measure will be continuous abstinence from smoking during weeks 9 – 12 as reported at clinic visits during those 4 weeks and confirmed using expired CO. Subjects will be classified as treatment responders if they respond “no” to the question: Have you smoked any cigarettes (even a puff) in the last seven days?

The key secondary outcome measures are:

1. Self-reported 7 day point prevalence abstinence throughout weeks 2 to 12 confirmed by expired CO at each clinic visit. To calculate survival curves we will also collect self-reported continuous abstinence weeks 9 through 26. For weeks 13 to 25, this will be collected via email or text message. For week 26, subjects will attend a brief clinic visit so abstinence can be confirmed with expired CO and urinary cotinine using a semi-quantitative dipstick. We hypothesize that the active tDCS group will have higher rates of abstinence (less relapse) than the sham tDCS group.

2. fMRI: change in Blood Oxygen Level Dependent (BOLD) activation in brain regions known to be associated with drug craving and emotion processing/regulation. MRS: GSH levels measured in a single voxel placed over prefrontal cortex. Fractional anisotropy (FA) values will be extracted from DTI analysis from regions of interest (ROIs) or to form probabilistic tractography for the whole brain. Network maps will be extracted and analyzed from the resting state functional connectivity measure.

3. Eye Tracking tests: changes in attentional bias to smoking-related cues and negative emotional cues. Attentional bias to high-arousal/high-risk cues.

*Self-Report Measures*

Participants will complete the 10-item Questionnaire of Smoking Urges-Brief (QSU-10; Tiffany and Drobes, 1991) and the Minnesota Nicotine Withdrawal Scale (MNSW; Toll et al, 2007) at each treatment session upon arrival and immediately after tDCS. They will complete a Side Effects Checklist ([name] et al., 1995) at the end of each treatment session.

Trait scales to be completed at baseline will include the FTND (Heatherton et al 1991) and Alcohol Use Disorders Identification Test (Saunders et al., 1993), 90-day Alcohol Timeline Followback (TLFB; Sobell and Sobell, 1992); 30-day Tobacco Timeline Followback (adapted from alcohol TLFB); Sensation Seeking Scale (Zuckerman et al., 1978).

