**Data Analysis**

Continuous data (cravings, mood, cigarettes smoked/day, CO) will be assessed with 2 Gender x 2 (Laterality) x 10 (session) Analyses of Variance (ANOVA). Parallel ANOVAs will assess self-report measures during post-treatment follow-up. Categorical data (e.g., # abstinent participants/session) will be assessed with chi-square, and Kaplan-Meyer survival analysis for repeated measures. Planned comparisons will be performed for the critical experimental conditions (active tDCS) vs. sham.

The critical metric will be Effect Size (partial η2 generated by SPSS), rather than p level. This will reveal the degree of efficacy for the primary outcome variable, Consecutive Days Abstinent (small = .01, medium = .06, large = .14), and allow us to estimate N required to achieve statistical significance for this effect (80% power, α = .05, two-tailed). Pearson correlations will explore the possible relationship between effects of tDCS (session 10 scores, controlling for session 1) and trait factors (e.g., FTND, age, gender, depression).Analysis of MRI data

For the neuroimaging data, brain imaging measures will be compared between groups and across time points, using analysis of variance. MRI measures will also be related to subjective responses (i.e., baseline scores and changes in craving, mood, and withdrawal) using linear regression.

fMRI data will be analyzed by fitting a general linear model (GLM) to the data time-series at every voxel across the brain (and/or within ROIs) and assessing effects using F/t-tests and % signal change calculations. Quantitative T1 maps and DTI analysis will be analyzed at the whole brain level and using ROIs.

After back-sorting by treatment outcome (achieved/maintained abstinence), we expect baseline measures to predict relapse, and active tDCS treatment to result in more efficient functional activation, . than sham tDCS at the second MRI scan.

Analysis of Eye-Tracking Data

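### The follow-up ANOVAs are modelled on a Gender x Laterality x 10-session template that does not fit a follow-up with a single continuous self-report occasion and that omits treatment arm

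*Protocol*

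**What the plan says.** Under Data Analysis, continuous data (craving, mood, cigarettes per day, CO) are to be analysed with "2 Gender x 2 (Laterality) x 10 (session) Analyses of Variance (ANOVA". The next sentence extends this to the period after treatment: "Parallel ANOVAs will assess self-report measures during post-treatment follow-up". It names no measures, time points or factors of its own. Active versus sham appears separately, as planned comparisons. Categorical data go to chi-square and Kaplan-Meier methods.

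What is collected after week 12 is described in several places:

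- **Design:** "For the next 14 weeks they will be contacted weekly by e-mail or text message to report on their smoking status". Each contact puts one yes/no item to the participant, on any smoking in the past week. At six months participants return "to confirm smoking abstinence using expired CO and urinary cotinine and to complete questionnaires".
- **Outcome Measures:** of the self-reported abstinence used for survival curves, "For weeks 13 to 25, this will be collected via email or text message"; week 26 is a brief clinic visit. The brief smoking-urges questionnaire (QSU-10) and the Minnesota withdrawal scale are given "at each treatment session upon arrival and immediately after tDCS".
- **Abstract, Measurements:** self-reported smoking, craving and withdrawal are listed for every study visit.
- **Eye Tracking and Free Viewing paradigm:** the fifth eye-tracking session is at six months, and every session is preceded by assessment of withdrawal, mood and craving, with the QSU and POMS named.
- **Monetary Delayed Discounting Task:** the 27-item questionnaire is completed at baseline, end of treatment and six months.

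**The concern.** An analysis parallel to the session ANOVA, applied within follow-up, needs a continuous measure taken on several follow-up occasions. The weekly contacts, which make up nearly all of the follow-up, carry only a yes/no answer. The other factors of the template also need checking against the design, because a model built on them is of use only if it contains the contrast the trial was set up to estimate.

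At stake is the follow-up comparison of craving, mood and withdrawal between active and sham tDCS. This is a non-primary analysis, but it bears on the research question about longer-term resistance to relapse. As worded, the sentence does not lead an analyst to an arm effect at six months.

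**Working it through.** The protocol gives no figure to reproduce here. The check is a count of occasions, followed by a comparison of the template with the design.

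**1. Occasions in follow-up.** Follow-up runs from week 13 to week 26: 26 − 13 + 1 = 14 weeks, as Design states. Weeks 13 to 25 are remote: 25 − 13 + 1 = 13 contacts. Week 26 is the one clinic visit.

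| Period | Occasions | Yes/no abstinence | Continuous self-report |
|---|---|---|---|
| Weeks 13–25 | 13 contacts | 13 | 0 |
| Week 26 | 1 visit | 1 | 1 |

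For contrast, treatment has 10 daily sessions plus 5 boosters = 15, which agrees with Participant compensation.

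**2. The template's factors at follow-up.** A factor with k levels contributes k − 1 degrees of freedom.

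- *Session.* During daily treatment k = 10, giving 9. Within follow-up k = 1, giving 0. There is no session effect and no interaction with session.
- *Laterality.* The template gives it two levels. Procedures places the anode over the left and the cathode over the right DLPFC for active and sham alike, and states that sham electrodes are placed identically. So k = 1, giving 0.
- *Gender.* k = 2, giving 1. This is the only factor left.
- *Arm.* Not in the template.

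Carried over literally, the follow-up ANOVA becomes a comparison of men with women on the week-26 score. If Laterality was meant to stand for active versus sham, the text does not say so.

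**3. What the schedule does support.** Counting earlier assessments as well as week 26:

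- Craving and mood alongside eye-tracking: baseline, weeks 4, 8, 12 and 26 = 5 occasions.
- Delay discounting: baseline, weeks 12 and 26 = 3 occasions.

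Both a baseline-adjusted comparison at week 26 and an arm-by-time analysis across visits are therefore feasible.

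**4. Which instruments are given at week 26.** The sections do not agree.

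- The Abstract implies craving, withdrawal and self-reported smoking.
- Design says only that questionnaires are completed.
- Free Viewing paradigm says withdrawal, mood and craving but names only the QSU and POMS.
- Outcome Measures ties the QSU-10 and the withdrawal scale to treatment sessions, which have ended by then.
- No instrument is named for cigarettes per day at week 26. The tobacco Timeline Followback is listed among the baseline scales.

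**The case against.** The strongest reply is that the sentence is loose, not wrong. An ANOVA of week-26 scores by arm is still an ANOVA. The week-26 scores repeat measures taken at baseline and end of treatment, so a time factor exists if those visits are included. The exact measures and time points of a secondary analysis are commonly left to a SAP, which is not shown. The trial is a 50-person pilot whose stated aim is to estimate an effect size.

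Much of this stands. A reader might infer that no repeated continuous data exist beyond treatment and that no ANOVA can be run. The documents do not support that, because the Abstract, Design, Free Viewing paradigm and Monetary Delayed Discounting Task sections all place continuous self-report at six months. A reader might also expect the weekly yes/no answers to be put through an ANOVA. That is not planned either: Outcome Measures collects abstinence for survival curves, and Data Analysis sends categorical data to chi-square and Kaplan-Meier.

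Nor is the content of the weekly message an error in this sentence. The item measures the outcome the protocol defines. It cannot show how much was smoked within a week, but asking for more is an optional design addition.

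What the reply does not remove is the mismatch of form. The protocol does more than leave details open. It fixes the follow-up model as parallel to a specific template, for a specific period, and the schedule and electrode placement do not supply that template's factors. The planned comparisons mention active versus sham but do not say how it enters the follow-up model.

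**Conclusion.** The point holds in limited form. Of the three template factors, two (session and Laterality) have a single level at follow-up, and treatment arm is absent. Continuous self-report exists at 1 of 14 follow-up weeks. That is a design choice and not a defect in itself, but it rules out a session factor confined to follow-up. A week-26 comparison by arm can be run with data already planned.

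This rests on two readings. The first is that parallel means the same factor structure, which is the natural meaning since no other structure is given. The second is that the six-month visit does include the craving, mood and withdrawal assessments implied by the Abstract and the Free Viewing paradigm section. If that visit were limited to the confirmation of abstinence and unspecified questionnaires, the set of comparable measures could be smaller. Neither the primary abstinence outcome nor the survival analyses are affected.

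**What to change.** Replace the sentence on parallel ANOVAs with a baseline-adjusted (ANCOVA) comparison of active with sham at week 26:

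- **Outcomes:** the continuous self-report measures collected at that visit, namely craving, mood and withdrawal, plus cigarettes per day if it is recorded there.
- **Model:** week-26 score on arm and the baseline score of the same instrument. No session or Laterality term.
- **Report:** the adjusted arm difference with its confidence interval, which suits a pilot meant to inform a later sample size. With correlation ρ between baseline and week 26, adjustment multiplies the residual variance by about 1 − ρ². The protocol gives no value for ρ, so the gain cannot be sized here.

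Reconcile Abstract, Design, Free Viewing paradigm and Outcome Measures so that they list the same instruments for the six-month visit. State which pre-treatment assessment is the baseline, since the session scales are taken both on arrival and after stimulation.

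Keep the weekly yes/no series in the planned categorical and survival analyses. A repeated-measures logistic model, or an extra weekly item on amount smoked, would be a matter of preference and is not needed to correct this point.

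The cost is a small change of analysis wording and a consistency edit. It needs no new visits.

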**Procedures**

Following the initial assessment appointment to obtain consent and confirm eligibility, the first tDCS treatment session will be booked. A breathalyser will screen for alcohol and expired CO at each tDCS session. The tDCS stimulation will take place in a quiet room, free of distractions. Stimulation will continue uninterrupted for 20 minutes with the experimenter in the room. While being stimulated, subjects will be required to read self-help materials related to smoking cessation, relapse prevention, and mood management. The readings for each day of stimulation will be standardized for all subjects.

To increase the opportunity to detect an acute beneficial effect of tDCS, participants will be asked to refrain from smoking for 2 hours prior to the start of each treatment session. Relative CO readings from the first day (ad lib smoking) compared to subsequent days will provide a coarse means of verifying compliance with the 2-hour pre-session smoke-free requirement.

Participants will be randomly assigned (1:1) to one of 2 treatment arms (double-blind). Participants will be matched as closely as possible on age, gender and cigarettes per day.

There will be 10 consecutive daily sessions of tDCS with the anode over the left DLPFC and cathode over the right DLPFC (active or sham) (Monday-Friday for 2 weeks; 2 mA x 20 min). Participants assigned to sham will have electrodes placed identically to active but receive only 30 seconds active stimulation. Participants will also be videotaped during each tDCS session to ensure consistency of tDCS application between research personnel and for documenting participant reactions during the session. This will also be used to document any side effects/complications participants may experience during the session. Each video tape session, as well as all data collected in the trial, will be stored on a secure server and will be retained for 10 years after the participant completes the study, as suggested by CAMH’s policy on Storage of Records. After each tDCS session, the video footage will be transferred from the camera to the secure server.

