**Sample Size and Power Calculation**

If we assume a 40% abstinence rate at end of treatment in the varencline plus sham tDCS group, the abstinence rate in the active tDCS group would need to be double that or 80% in order to see a statistically significant difference with n=25 per arm, p <0.05, and 80% power. As such we do not expect to see a statistically significant difference between the two treatment arms at 25 subjects per arm.

For the treatment part of the study, the main purpose of the study is to establish an Effect Size for tDCS as an adjunct to standard varenicline treatment. This is independent of the number of subjects but allows us to estimate the N that would be required to achieve statistical significance depending on the effect size we observe. The effect size measure we will use will be the partial η2 generated by SPSS and is described in greater detail below.

For the MRI portion of the study, 15 to 25 subjects per group is standard in the neuroimaging field and is more than sufficient to detect significant within- and between-group differences in brain activity.

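### The abstinence analyses ignore the three factors on which the arms are matched, so the test may be mildly conservative; adjusting for them is a cheap improvement

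*Protocol*

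**What the plan says.** Under Procedures, the protocol assigns participants at random, 1:1 and double-blind, and adds: "Participants will be matched as closely as possible on age, gender and cigarettes per day". It does not describe how the matching is combined with randomisation (strata, pairs or minimisation).

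Under Outcome Measures, "The primary outcome measure will be continuous abstinence from smoking during weeks 9 – 12", which is a yes/no outcome.

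Under Data Analysis, the text for such outcomes is: "Categorical data (e.g., # abstinent participants/session) will be assessed with chi-square, and Kaplan-Meyer survival analysis for repeated measures". No covariate or stratum is named. Continuous measures "will be assessed with 2 Gender x 2 (Laterality) x 10 (session) Analyses of Variance (ANOVA"), so gender enters there, but age and cigarette consumption do not. Age and gender appear again only among the trait factors for exploratory Pearson correlations. The Cox regression described for the eye-tracking data concerns scanning parameters. No between-arm analysis of abstinence uses the matching factors.

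Under Sample Size and Power Calculation, the design figure is 25 per arm: "If we assume a 40% abstinence rate at end of treatment in the varencline plus sham tDCS group", against 80% in the active arm, with 80% power. The section adds that significance is not expected and that the main aim is an effect size from which to plan a later trial.

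**The concern.** When allocation forces the arms to be alike on factors that predict the outcome, part of the chance variation between arms is removed by design. An unadjusted chi-square does not know this. Its standard error still includes the removed variation, so it is too large, and the test rejects less often under the null than it otherwise would.

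At stake is how well the trial uses its 50 participants. It takes the trouble to match, and measures the factors at baseline, but does not carry them into the analysis of its main binary outcome. The result is meant to feed the sample size of a later trial, so an uncertainty statement that reflects the allocation would be useful.

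**Working it through.** **1. The plan's own figure.** Inputs from Sample Size and Power Calculation: 40% v 80%, 25 per arm, α 0.05, 80% power. Two-sided testing is stated under Data Analysis for the later trial's size.

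Pooled formula, mean rate 0.6: n = [1.96·√(2·0.6·0.4) + 0.842·√(0.4·0.6 + 0.8·0.2)]² / 0.4² = (1.358 + 0.532)² / 0.16 = 22.3, so 23 per arm. At 25 per arm, power is 84.5% by this approximation, 86.7% by the uncorrected chi-square (exact enumeration) and 78.8% by Fisher or the continuity-corrected chi-square. The stated 25 is reproduced closely enough.

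**2. Large-sample effect of ignoring perfectly balanced factors.** Let R² be the share of outcome variance that the three factors explain. The documents give no value, so a range is assumed. The true SE is √(1−R²) times the nominal SE. The true two-sided error of a nominal 5% test is 2[1 − Φ(1.96/√(1−R²))].

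| R² | SE too large by | True error |
|---|---|---|
| 0.05 | 2.6% | 4.4% |
| 0.10 | 5.4% | 3.9% |
| 0.20 | 11.8% | 2.8% |
| 0.30 | 19.5% | 1.9% |

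These are upper limits, because real matching in 50 people is not perfect.

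**3. Simulation at the trial's size.** N = 50, biased-coin minimisation on gender and on two continuous factors cut into thirds, 4,000 trials per row. The uncorrected chi-square is compared with a linear risk-difference regression on arm plus the three factors. Entries are unadjusted / adjusted.

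| R² | Null rejection, % | Power 40 v 60, % | Power 40 v 80, % | True SD of difference, 40 v 80 |
|---|---|---|---|---|
| 0 | 6.1 / 5.0 | 34.7 / 29.8 | 87.4 / 84.5 | 0.1228 / 0.1243 |
| 0.045 | 5.8 / 4.9 | 33.7 / 31.8 | 87.5 / 86.3 | 0.1248 / 0.1252 |
| 0.145 | 4.5 / 4.8 | 31.9 / 31.4 | 88.1 / 89.2 | 0.1205 / 0.1186 |
| 0.29 | 3.5 / 5.3 | 30.3 / 36.4 | 88.8 / 93.0 | 0.1152 / 0.1111 |

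Mean unadjusted SE over true SD:
- At R² 0.145: 0.1360/0.1306 = 1.04 under the null and 0.1237/0.1205 = 1.03 at 40 v 80.
- At R² 0.29: 0.1360/0.1248 = 1.09 and 0.1241/0.1152 = 1.08.

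A further run of the same kind at 40% v 70–80% gave:
- R² 0.25: null error 3.8%, SE about 8% too large, gain 3–5 power points, true SD 0.115 raw v 0.112 adjusted.
- R² 0.16: gain about 2 points.
- R² 0.10: about nil.
- R² 0.05 or below: a cost of 1–4 points.

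**4. Reading the results.** At R² 0.25 the large-sample formula gives 1/√0.75 = 1.155, or 15.5%, about twice the simulated 8%. With no predictive factors, the uncorrected chi-square at 40% in both arms of 25 already rejects 6.0% of the time by exact enumeration. Part of the apparent cost of adjustment at low R² is therefore the unadjusted test running above its nominal level. The continuity-corrected version rejects 2.9% of the time, before any effect of matching.

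**The case against.** The strongest objection is that matching has already done the work. In a simulation with pairs formed on the prognostic score itself and adjustment for its three components, the true SD of the difference at 40% v 80% was 0.113 raw and 0.116 adjusted at a factor–outcome correlation of 0.5 (R² 0.25). Power, raw v adjusted, was 87.2% v 84.9% at correlation 0.2, 87.1% v 86.1% at 0.3, 89.1% v 89.0% at 0.4 and 89.7% v 91.4% at 0.5. This stands, with the caveat that pairing on the exact score favours the raw estimate.

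It also rules out some stronger readings:

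- A reader might infer that the unadjusted difference is biased or materially less precise. Under close matching it is neither. Precision is really lost under plain randomisation (SD 0.127 raw v 0.116 adjusted at correlation 0.5), but then the unadjusted SE suits the allocation and the mismatch disappears.
- A reader might apply the 1−R² rule at R² 0.25 and infer that power rises from 80% to about 90%: (1.96 + 0.84)/√0.75 − 1.96 = 1.27. The simulations at this sample size show 3–5 points.
- A reader might infer that a reported interval would be too wide, or that chi-square is the sole abstinence analysis. The protocol plans no interval for abstinence. It also names Kaplan-Meier and an effect-size analysis of consecutive abstinent days.

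Two further objections carry weight. The protocol ranks effect size above the p value, so a slightly conservative p value touches its aim only lightly. Covariate choice is also often left to a statistical analysis plan, which may exist. Against the second, the protocol does name the test, so any adjusted analysis elsewhere would have to be reconciled with this sentence.

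**Conclusion.** The point holds as a modest efficiency improvement. The arms are matched on three factors that the chi-square and Kaplan-Meier analyses of abstinence leave out. If those factors predict abstinence, the SE behind the unadjusted test is too large and the test is mildly conservative. Validity is not threatened.

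The size rests on an R² that the documents do not give, and on matching that works roughly like minimisation. Only at R² of about 0.16 or more does adjustment bring a visible gain: about 2 points at 0.16, and 3–5 points at 0.25, where type I error is about 3–4%. Around 0.10 there is nothing to choose, and at 0.05 or below adjustment may cost 1–4 points. Looser matching would shrink the conservatism, while adjustment would then improve the estimate itself.

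**What to change.** In the Data Analysis section, make the analysis of weeks 9–12 abstinence a regression on arm plus the three matching factors (age, gender and baseline cigarette consumption). Report the risk difference standardised over the trial's participants, with its 95% confidence interval. Keep the unadjusted chi-square as a sensitivity analysis.

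Limit the covariates to these three. FTND is also measured at baseline ("Trait scales to be completed at baseline will include the FTND"), but with 50 participants it should stay out of this model. State the model form in advance. The simulations above used a linear risk-difference model; a logistic model with standardisation was not simulated.

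The cost is a change of wording, three degrees of freedom, and a small loss of power if the factors turn out to be weak predictors. No new data are needed. If a statistical analysis plan already specifies such a model, the protocol sentence need only be brought into line with it.

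### Two different variables are each called the primary outcome, and the trial's main product, an effect size for a later N, is tied to the one that is not defined

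*Protocol*

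**What the plan says.** Protocol, Outcome Measures: "The primary outcome measure will be continuous abstinence from smoking during weeks 9 – 12", reported at clinic visits and confirmed by expired CO. A yes/no rule follows, beginning "Subjects will be classified as treatment responders if they respond", and it depends on a no to a seven-day smoking question.

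Protocol, Sample Size and Power Calculation: the power statement uses abstinence rates, starting "If we assume a 40% abstinence rate at end of treatment in the varencline plus sham tDCS group" and setting 80% against it with 25 per arm. The section then concedes that significance is not expected and gives establishing an effect size, from which a later N can be estimated, as the main purpose of the treatment part.

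Protocol, Data Analysis: "The critical metric will be Effect Size (partial η2 generated by SPSS), rather than p level". The next sentence reads "This will reveal the degree of efficacy for the primary outcome variable, Consecutive Days Abstinent", adds the bands "small = .01, medium = .06, large = .14", and states the use: "allow us to estimate N required to achieve statistical significance for this effect". The same section sends categorical abstinence data to chi-square and Kaplan-Meier methods.

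**The concern.** Outcome Measures and the power statement rest on the proportion abstinent. Data Analysis gives the primary label to a count of days. The count is named nowhere else in the protocol. It is not stated when it starts, over which period it runs, whether it is the longest run or the run from the quit date, what ends it, whether CO must confirm it, or which record supplies it.

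In a trial that expected a significance test to decide the question, this would be a familiar conflict of endpoints. Here it reaches further, because the effect size and the N derived from it are the declared product. If two variables can each be called primary, two effect sizes can each be reported as the result, and nothing in the protocol prevents the choice from being made once both are known.

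**Working it through.** **1. Which variable does the power statement use?** Inputs from Sample Size and Power Calculation: p₁ = 0.40, p₂ = 0.80, 25 per arm, α = 0.05, 80% power. The test is taken as two-sided, as Data Analysis states for the later N. With p̄ = 0.60:

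n = [1.960·√(2·0.60·0.40) + 0.8416·√(0.40·0.60 + 0.80·0.20)]² / 0.40² = (1.358 + 0.532)² / 0.16 = 22.3, so 23 per arm (28 with continuity correction).

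Power at 25 per arm is 84.5% by the normal approximation, 86.7% by exact enumeration for the uncorrected chi-square test, and 78.8% for Fisher's test. The plan's figure therefore reproduces as a comparison of two proportions. No mean or SD of days enters it.

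**2. The sections side by side.**

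| Section | Variable | Type |
|---|---|---|
| Outcome Measures | Abstinence in weeks 9 to 12, CO-confirmed | Yes/no |
| Sample Size and Power Calculation | Abstinence rate at end of treatment | Proportion |
| Data Analysis | Consecutive Days Abstinent | Day count, undefined |

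**3. Are these two names for one variable?** No. The target quit date is the end of week 2. Take the count as the longest run during treatment (one possible reading). A participant abstinent from the end of week 2 to the end of week 8 who lapses in week 9 scores 6 × 7 = 42 days and fails the weeks 9 to 12 outcome. A participant who stops only at the start of week 9 and holds to the end of week 12 scores 4 × 7 = 28 days and passes. The two variables rank these participants in opposite order.

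**4. Effect size on the binary outcome.** For two equal arms, η² = ((p₂ − p₁)/2)² / (p̄(1 − p̄)). For 40% versus 60%: 0.10² / (0.50·0.50) = 0.040. N per arm uses the formula in step 1.

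| Active rate (sham 40%) | η² | N per arm |
|---|---|---|
| 50% | 0.010 | 388 |
| 60% | 0.040 | 97 |
| 65% | 0.063 | 62 |
| 70% | 0.091 | 42 |
| 80% | 0.167 | 23 |

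**5. Effect size on the day count.** With d = 2√(η²/(1 − η²)) and n = 2(1.960 + 0.8416)²/d², the protocol's bands of 0.01, 0.06 and 0.14 imply 389, 62 and 25 per arm. Nothing in the protocol says which band a given change in abstinence rate would produce on days.

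An illustration needs assumptions, none of which comes from the protocol except the window of 10 weeks × 7 = 70 days after the quit date. Weeks 9 to 12 quitters were given a run of 70 days minus an exponential delay (mean 10, at most 42). Non-quitters were given an exponential run (at most 60 days), with mean 7 in sham.

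| Binary effect | Mean run, active non-quitters | η² on days | N per arm from days |
|---|---|---|---|
| 40% v 60% (97 per arm) | 7 days | 0.036 | 105 |
| 40% v 60% | 14 days | 0.061 | 60 |
| 40% v 60% | 21 days | 0.087 | 42 |
| 40% v 40% (none) | 14 days | 0.006 | 651 |
| 40% v 40% | 21 days | 0.022 | 177 |

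One and the same binary effect gives different values of N, and no binary effect can still give a finite N.

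**The case against.** The best case for the plan is that this is a drafting slip in a pilot. The Background calls the study a proof of concept, significance is not expected, and the p level is expressly made secondary. The Hypotheses and the eye-tracking analysis both group quitters by the last four weeks of treatment, which points to weeks 9 to 12 abstinence as the intended outcome. Duration of abstinence is also not foreign to the plan: the first key secondary outcome collects abstinence over weeks 9 to 26 for survival curves, and the eye-tracking analysis uses time to relapse. All of this stands and bears on how the conflict arose. It does not remove it, because no section says which label prevails. A separate analysis plan could add detail, but the protocol would still contradict itself.

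A reader might also infer more than the documents support:

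- That a day count cannot be built. The only named day-level tool, the tobacco timeline follow-back, is listed at baseline, and weeks 13 to 25 use a weekly seven-day question. But the Abstract takes self-reported smoking at each visit, the Pharmacological treatment section documents smoking behaviour at booster visits, and Data Analysis lists cigarettes per day. The source is unspecified, not shown to be missing.
- That the day count is an unplanned analysis. Data Analysis plans it. It is simply not the outcome defined in Outcome Measures or the rate used for power.
- That no conversion to rates exists, or that the later N would be meaningless. A conversion needs an assumed distribution. If the later trial itself used days, N would follow from η² directly, and the protocol does not name that trial's endpoint.
- That the count piles up at zero and at the maximum, so that ANOVA fails. This is a reasonable expectation, but the protocol gives no distribution.
- That a confirmatory type I error rate is inflated. No confirmatory claim is made.

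**Conclusion.** The contradiction is on the face of the protocol and must be resolved before outcome data are examined. Outcome Measures and the power statement concern abstinence as yes/no; Data Analysis gives the primary label, the critical metric and the later N to an undefined day count. What is at stake is which effect size is reported as the trial's result.

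The size cannot be fixed from the protocol, which gives no mean or SD for days. Under the assumed distributions above, an effect of 40% versus 60% that needs 97 per arm on the binary outcome gives 42 to 105 per arm on days. These figures show only that N can move. The η² of 0.167 for 40% versus 80% is the power statement's own contrast on another scale and does not measure the defect.

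**What to change.** In Data Analysis, replace Consecutive Days Abstinent with the outcome in Outcome Measures, CO-confirmed abstinence in weeks 9 to 12, as the sole primary. Report the active-minus-sham risk difference, with the odds ratio, and a 95% CI in all randomised participants. Derive the later N from the proportions. Bring the effect-size sentence in Sample Size and Power Calculation into line, since it also names partial η².

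Either delete Consecutive Days Abstinent or list it in Outcome Measures as a secondary outcome, with start date, window, lapse rule, CO rule and a data source already collected. A rank-based analysis is then optional.

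While editing, also settle how the seven-day responder question establishes four weeks of abstinence: with visits every two weeks, two such answers cover 14 of 28 days. Naming one primary does not by itself settle that.

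The cost is protocol wording. No new data are needed if the count is deleted, or if it is kept and a suitable record is already being taken at visits.
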